**Fig. 2 Fig2:**
[figure not shown]
Mulligan Manual Therapy techniques

#### Technique 1

Headache SNAG: A posteroanterior mobilisation of the second cervical vertebrae is sustained for 10 to 30 s with the aim to reduce headache intensity at the time of application. A maximum of 6 repetitions will be given if there is a reduction in headache at the time of the first application [44].

#### Technique 2

Reverse Headache SNAG: In the event of a failed response in terms of pain reduction to a Headache SNAG, an anteroposterior mobilisation of the second cervical vertebrae is sustained for 10 to 30 s depending on response. A maximum of 6 repetitions will be given if there is a reduction in headache intensity at the time of the first application [44]. Both of the above interventions will be delivered with the patient in a comfortable sitting position while the therapist cradles the participant’s head with one hand while the other hand applying the mobilisation force [44].

#### Technique 3

Modified headache SNAG to C3: In the event of a failed response to a Headache SNAG, and Reverse Headache SNAG, a posteroanterior mobilisation of the third cervical vertebrae is sustained for 10 to 30 s depending on response. A maximum of 6 repetitions of the successful technique will be given if there is a reduction in headache at the time of the first application [34].

#### Technique 4

Upper cervical traction: In the event of a failed response in terms of pain reduction to the previous techniques, upper cervical traction will be delivered with the participant in a supine position. The therapist pronates their forearm against the subject’s occiput while fixing the subject’s chin. The resultant traction force will be sustained for 10–30 s with the aim to reduce headache intensity. A maximum of 10 repetitions will be delivered in a single session [44].

#### Technique 5

C1-C2 SNAG: If the subject does not present with a headache at the time of the assessment, the flexion-rotation test (FRT) [45] will be evaluated. If a 10° restriction is identified compared to the reference standard of 44°, a unilateral posteroanterior mobilisation will be applied to the transverse process of the first cervical vertebrae on the contralateral side of restriction on the FRT. The subject will be asked to rotate the head towards the restricted side of the flexion-rotation test as far as they are able without pain. A maximum of 3 repetitions will be applied in a single treatment session. If impairment is not identified on the FRT and there is no headache symptoms present, then only exercise will be provided as there is no further option for treatment using MMT.

The third group will receive a placebo replicating the Headache SNAG technique but without any manual force applied. The position will be held for 10 to 30 s and 6 repetitions applied. The duration of the placebo treatment session will be similar to that in the MMT group. Participants will continue to receive the same exercise protocol as the other groups. Any increase in headache intensity or neck pain for more than 1 h or dizziness during or after the intervention will be documented as an adverse event. In such cases, participants will be referred to a medical practitioner of the hospital and withdrawn from the study.

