**Methods:**

This pragmatic trial is designed as a prospective, three-armed randomised controlled trial in a clinical setting provided at a general hospital physiotherapy department. Two hundred ninety-seven participants with a diagnosis of migraine, TTH or CGH based on published headache classification guidelines will be included. An assessor blind to group allocation will measure outcomes pre-and post-intervention as well as 3 and 6 months after commencement of treatment. Participants will be allocated to one of the three groups: MMT and exercise; placebo and exercise; and exercise alone. The primary outcome measure is headache frequency. Secondary outcome measures are headache duration and intensity, medication intake, pressure pain threshold (PPT), range of motion recorded with the flexion rotation test, and headache disability recorded with Headache Activities of Daily Living Index (HADLI). The intention-to-treat principle will be followed for statistical analysis. Between groups differences for all outcome measures at baseline and at reassessment points and 95% confidence intervals will be calculated using a mixed model ANOVA. Post hoc tests will be conducted to identify any significant difference between groups and over time.

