### Interventions

Each subject will receive 6 treatment sessions spread over 4 consecutive weeks and each treatment session will not extend beyond 30 min. A principal investigator will perform all the interventions. The principal investigator is a physiotherapist with a Masters degree in musculoskeletal physiotherapy with 15 years of clinical experience who has undertaken the highest level of training in MMT.

All participants will be informed that their designated intervention has been shown to improve headache symptoms. Treatment will cease if the subject withdraws consent, has an increase in pain or discomfort due to the treatment, or develops any contra-indication during the intervention period. Additionally subjects will be withdrawn if they receive any other physiotherapy program including massage, manual therapy or chiropractic treatment to the neck or shoulder region. All participants will be requested to avoid any forms of manual therapy or massage until the final evaluation at 6 months.

All participants will receive the following structured exercise programme encompassing conventional cervical flexion loading exercise [42], upper quarter low load endurance training, stretching, and generalized mobility exercises [43]. All exercises will be supervised during each session and exercise parameters will be adjusted if required but without any modifications in the type of exercise.

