### Outcomes

Outcome measures will be taken at base line just after enrolment, as well as at 4 weeks, 3 months and 6 months following treatment commencement by an assessor, blind to group allocation and intervention. To assess whether the participants were blind to intervention or not, after each treatment session the participants in the MMT and the placebo group will complete a questionnaire on whether they believed MMT treatment was received, partly received or not.

The primary outcome measure is headache frequency [46] which is the total number of headache days per month noted in a headache diary. Secondary outcome measures are as follows: headache intensity [47] recorded on a 10 cm visual analogue scale, which is considered a valid and reliable tool for measuring pain intensity [47]. Headache duration [46] will be measured in hours per week. Headache frequency and duration are considered a valid method of measurement in the headache population [46]. Medication Intake will be recorded as total tablets consumed per week. PPT will be measured using a digital algometer with a surface area of 1 cm kg/cm^2^, with pressure applied at the rate of 1 kg/ cm^2^ /s perpendicular to the skin. PPT will be assessed over the suboccipital muscles, C2–3 zygapophyseal joint and upper trapezius muscle bilaterally [48] to assess local hypersensitivity, and over the tibialis anterior muscle to assess central sensitisation. Reliability for measuring PPT was reported as excellent (ICC: 0.82–0.99) [49]. Headache disability will be recorded with the Headache Activities of Daily Living Index (HADLI) [50] which is a 9 item self-reported questionnaire designed to measure the impact of headache on quality of life. Each item has 6 sub-questions which are rated from 0 to 5 thus the maximum score of 45 indicates a severe disability. Patient satisfaction will be assessed using a 0–100% numeric rating scale. Passive upper cervical rotation range in degrees to both sides will be measured with the FRT using a previously reported reliable and valid method [45]. A compass application on a smart phone mounted on the patient’s head with Velcro straps will be used to measure range of motion. Reliability of the FRT was reported as good to excellent in subjects with migraine (0.71–0.78) and CGH (ICC: 0.73–0.83) [51].

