### Statistical methods

The sample size for this study was calculated based on the primary outcome of headache frequency. According to the International Headache Society guidelines (2018), a 50% reduction in headache frequency is considered a clinically significant difference. A sample size of 297 participants will be required for the study based on a priori power analysis with a power of 0.8 and an alpha of 0.05 assuming 10% drop-outs.

All data entry will be carried out by research assistants who will be blind to treatment allocation. The final trial dataset will be accessible to all investigators and a statistician. Data will be stored with the principal investigator. Descriptive statistics will be performed to examine baseline parameters and demographic data. Demographic data will include age, gender, symptom duration, occupation, height, and weight. Baseline parameters will include the headache frequency, intensity, duration, medication intake, PPT, HADLI score, and FRT range of motion. Parametric tests will be used for normal distributions and ratio level data. Between groups differences for the primary and secondary outcome measures at baseline and at reassessment points and 95% confidence intervals will be calculated using mixed ANOVA. Post hoc tests will be conducted to identify any significant difference between groups and over the time. The intention-to-treat principle will be used if loss of follow up is not more than 10%. Non-parametric tests will be applied for non-normal distributions and ordinal level data.

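### Participants with a listed adverse event leave the study rather than only treatment, so those withdrawn during treatment would have no post-baseline primary-outcome data

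*Protocol article*

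**What the plan says.** All references are to the protocol article.

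- **Adverse-event rule** (Interventions, last paragraph, after Technique 5), on a rise in these symptoms: "headache intensity or neck pain for more than 1 h or dizziness during or after the intervention will be documented as an adverse event". The consequence follows at once: "participants will be referred to a medical practitioner of the hospital and withdrawn from the study". The rule stands in the paragraph on the placebo group but is worded for participants in general. I read it as applying to all three arms.
- **Stopping rule** (Interventions, second paragraph): "Treatment will cease if the subject withdraws consent", or if the participant "has an increase in pain or discomfort due to the treatment, or develops any contra-indication during the intervention period".
- **Treatment period** (Interventions): "6 treatment sessions spread over 4 consecutive weeks".
- **Assessments** (Outcomes): baseline, then "at 4 weeks, 3 months and 6 months following treatment commencement". The primary outcome is headache days per month from a diary.
- **Analysis principle**: the Abstract says "The intention-to-treat principle will be followed for statistical analysis". Statistical methods makes this conditional: "The intention-to-treat principle will be used if loss of follow up is not more than 10" per cent.

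**The concern.** Stopping treatment and leaving the study are different acts. For harm, the stopping rule speaks only of treatment ending. The adverse-event rule goes further and takes the participant out of the study.

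An analysis that aims to follow intention to treat needs outcomes from everyone randomised, including those who reacted badly to treatment. Here the protocol itself directs that such people leave, on a trigger that includes worse headache, the condition under study. The trigger may also occur at different rates by arm: MMT uses sustained manual force, while the placebo copies the hold without force. If those who leave would have had worse headache frequency, and more of them leave one arm, the comparison among those who remain is tilted. An analysis plan can choose how to handle missing data, but it cannot recover outcomes that were never collected.

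**Working it through.** **Step 1. What is lost, and when.** Set the treatment period beside the visit schedule.

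| Time of withdrawal | Assessments lost |
|---|---|
| Before the 4-week visit | 4 weeks, 3 months, 6 months (all post-baseline) |
| After the 4-week visit, before 3 months | 3 months, 6 months |

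All six sessions fall within the first 4 weeks, so an event that arises in the treatment period normally puts the participant in the first row.

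**Step 2. The plan's own figure.** The sample size of 297 cannot be rebuilt, because the article gives no SD, baseline mean or control-arm change. Only the drop-out step can be checked: 267 / (1 − 0.10) = 296.7, rounded up to 297, which is 89 evaluable and 99 randomised per arm. This point does not depend on the figure. It serves as a scale: with 89 per arm, 80% power and two-sided alpha 0.05 (sidedness assumed), the detectable pairwise difference is (1.96 + 0.84) × √(2/89) = 0.42 SD.

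**Step 3. Possible bias in the between-arm comparison.** Let pT and pC be the shares withdrawn for an adverse event under MMT and in each comparator arm. Let Δ be the amount, in SD, by which withdrawn participants would have had worse headache frequency than those retained, taken as the same in each arm. The mean for all randomised in an arm is the retained mean plus p × Δ. If only retained participants are analysed, then

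bias in favour of MMT = (pT − pC) × Δ.

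The documents give none of these inputs. All values below are assumptions. Number withdrawn = 99 × pT + 2 × 99 × pC.

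| pT | pC | Withdrawn | Bias, Δ = 0.5 SD | Bias, Δ = 1 SD |
|---|---|---|---|---|
| 5% | 5% | 14.9 | 0 | 0 |
| 5% | 2% | 8.9 | 0.015 | 0.03 |
| 10% | 2% | 13.9 | 0.04 | 0.08 |
| 20% | 5% | 29.7 | 0.075 | 0.15 |

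If more participants leave a comparator arm than the MMT arm, the sign reverses. If Δ is zero, there is no bias at any rate. At 5% against 2%, the bias is 0.015/0.42 to 0.03/0.42, about 4% to 7% of the detectable difference.

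**The case against.** **Loose wording.** The article may not separate the terms carefully. Its sentence on treatment ending also covers withdrawn consent, and the next sentence withdraws people who receive other physiotherapy. This is fair, but the adverse-event rule names the study explicitly. If only treatment was meant, the correction is a change of words.

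**Trigger and outcome differ.** A flare in intensity lasting over an hour, or dizziness, does not show a poor response in headache days per month. This stands. Informative loss is possible, not shown, and a reader who infers that outcome data are known to be lost selectively from those harmed goes further than the text.

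**Intention to treat is an analysis principle.** Withdrawn participants can be included through missing-data methods, which a protocol article may leave to the analysis plan. This also stands, so the rule does not contradict the Abstract outright. It does leave such methods with no post-baseline data for these people.

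**Few events.** The Discussion says that earlier MMT studies of the upper cervical spine reported no adverse events. The low end of the range is therefore possible.

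Three further inferences are tempting but unsupported:

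- That some harms which stop treatment go unrecorded, because the adverse-event list is narrower than the stopping rule. A stopping threshold may properly sit below a reporting threshold. The list is not said to be exhaustive, and a condensed article commonly leaves full adverse-event definitions to the full protocol.
- That these withdrawals would trip the 10% condition on intention to treat. The limit would be passed at 30 of 297 (10.1%; 29 is 9.8%) from all causes, but the article does not say whether these withdrawals count as loss to follow-up.
- That the hypothesised 50% reduction in the MMT arm would be inflated by a known amount. That is a within-arm figure under assumed rates. The trial compares arms, where similar losses would partly or wholly cancel.

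**Conclusion.** The point holds for the withdrawal rule. As written, a participant withdrawn during treatment for a listed adverse event would have no post-baseline primary-outcome data, and no shown text provides for continued assessment. The loss may be informative and may differ by arm, which fits poorly with the intention-to-treat aim in the Abstract.

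The size and direction of any bias are unknown. Under the assumed rates above it runs from nil to 0.15 SD, and the upper end needs one MMT participant in five to be withdrawn. The conclusion rests on reading the rule literally and as covering all arms; the illustration also assumes that only retained participants are analysed. The case for change is that the rule creates an avoidable risk of bias and is cheap to correct, not that a large bias is expected.

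**What to change.** In the last paragraph of Interventions, keep documentation of the event and mandatory referral to a medical practitioner. Referral should stay mandatory, since making it discretionary would weaken a safety provision. Replace the words that remove the participant from the study with: *study treatment is stopped and outcome assessments continue at 4 weeks, 3 months and 6 months unless consent is withdrawn*.

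The cost is a few more follow-up visits, all already in the schedule. Sample size, arms and outcomes are unchanged.

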### Procedures

Participants will be provided with an information sheet outlining the study protocol including duration of commitment, intervention, benefits and harms of the treatment, voluntary participation, right to withdraw, as well as confidentiality of data. It will be explained that no compensation will be given if any adverse event occurs and study findings may be published but without revealing participants identity.

Those willing to participate will be enrolled and asked to provide signed written informed consent with the right to withdraw at any time. After recruitment, at initial assessment, a qualified therapist will explain the study procedures and collect demographic data. Confidentiality will be maintained throughout the trial.

Participants will then be randomly and equally allocated to one of three groups: MMT plus exercise; placebo plus exercise; or exercise alone by stratified randomization based on the type of headache. Randomization will be achieved using a computer-generated sequence received in advance from an independent statistician and will be hidden in sequentially numbered opaque sealed envelopes by a research assistant. All participants will be asked to not reveal their group identity and are advised to continue with their regular medical management. Any change in the protocol will be communicated with the ethics committee and if approved appropriate changes will be made in the Clinical Trial Registry.

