## Discussion

To our knowledge, this will be the first pragmatic RCT to evaluate the effects of MMT in the management of migraine, TTH and CGH. A pragmatic effectiveness study design will enable a greater understanding of the true effect of MMT when compared with a placebo intervention and a control group in reducing various parameters of headache over a 6 months period. A placebo effect is associated with all physiotherapy interventions however its contribution may vary. This study will help us to understand the true net effect of MMT over placebo.

Recruitment will be a challenge due to the strict inclusion criteria but that could be strength of our study to involve a homogeneous population of headache sufferers with features of upper cervical articular dysfunction who might respond to MMT.

Previous studies using MMT targeting the upper cervical spine for headache management have not reported adverse events associated with its application. Thus this approach appears to be safe for its clinical use [52]. All participants will continue to take their medications as prescribed by their medical practitioner.

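### The adverse-event rule withdraws participants from the study rather than only from treatment, and nothing keeps them in follow-up

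*Protocol article*

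**What the plan says.** Three rules in the Interventions section of the protocol article bear on this point.

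- **Adverse events** (closing paragraph, after Technique 5). The trigger is "Any increase in headache intensity or neck pain for more than 1 h or dizziness during or after the intervention". Such events are documented as adverse events, and "participants will be referred to a medical practitioner of the hospital and withdrawn from the study".
- **Stopping treatment** (second paragraph). Treatment ends if consent is withdrawn, if pain or discomfort rises because of the treatment, or if a contraindication develops. Leaving the study is not mentioned.
- **Other care** (same paragraph). "subjects will be withdrawn if they receive any other physiotherapy program including massage, manual therapy or chiropractic treatment to the neck or shoulder region". The next sentence adds: "All participants will be requested to avoid any forms of manual therapy or massage until the final evaluation at 6 months".

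The Outcomes section sets assessments at baseline, 4 weeks, 3 months and 6 months. It does not mention participants who stop or are withdrawn.

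On analysis, the abstract says "The intention-to-treat principle will be followed for statistical analysis". Statistical methods is narrower: it applies intention-to-treat only while loss to follow-up stays at or below 10%.

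**The concern.** Stopping an intervention for safety is a clinical decision. Ending outcome collection is a separate one, and the adverse-event rule ties the two together.

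The trigger overlaps what the trial measures. Headache intensity is a secondary outcome and is plausibly related to headache days, the primary outcome. Entrants have headache at least weekly, intensity above 6 on the visual analogue scale, and headache reproduced by neck palpation. In such people, more than an hour of worse headache after a session can be the ordinary course of the disease. The rule as written does not require attribution to treatment and sets no limit on how long after a session the event counts.

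The arms also differ in exposure: manual force with MMT, hand position without force in the placebo arm, and no manual contact with exercise alone. If withdrawal differs by arm and is related to outcome, the retained groups are no longer the randomised groups. An analysis plan cannot recover outcomes that were never collected.

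**Working it through.** **1. Is it withdrawal from treatment or from the study?** The article uses separate terms. One rule ends treatment when pain increases because of it; the adverse-event rule names the study. The same increase in pain can therefore meet two rules with different consequences, and the stronger rule lacks the attribution condition.

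**2. Does other text keep these participants in follow-up?** No. The Outcomes schedule makes no provision for them. The intention-to-treat sentences concern analysis, not data collection. All sessions fall within the first four weeks and the first post-baseline assessment is at 4 weeks. Someone withdrawn after a session before that visit would have no post-baseline assessment, only diary entries up to that date.

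**3. The other-care rule.** It does not say what the participant is withdrawn from. Treatment ends at 4 weeks, while avoidance is requested to 6 months. If the rule applies after week 4, there is no treatment left to stop, so withdrawal could only mean leaving the study. Whether it applies then is not stated.

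**4. Scale of the trial.** There are 297 participants in three equal arms: 297/3 = 99 per arm. The stated total cannot be reproduced in full, because no SD, baseline rate or between-group difference is given. The drop-out step alone is consistent: 267/0.9 = 296.7, or 297, which is 89 evaluable per arm (270 × 1.1 also gives 297). With two-sided alpha assumed, 89 per arm at 80% power detects (1.960 + 0.842) × √(2/89) = 0.42 SD.

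**5. Illustrative bias.** Assumptions: normal outcome, no true effect, the worst fraction f on the trigger removed, and trigger-outcome correlation r from 0.3 to 1. The shift in the retained mean is r × φ(z)/(1 − f), where z is the (1 − f) normal quantile.

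| Removal | Calculation at r = 1 | Shift, r = 0.3 to 1 |
|---|---|---|
| 5% of one arm (about 5 of 99) | 0.1031/0.95 = 0.109 | 0.03 to 0.11 SD |
| 10% of one arm (about 10 of 99; 9.9/297 = 3.3% of the trial) | 0.1755/0.90 = 0.195 | 0.06 to 0.20 SD |
| 10% in one arm, 5% in the other | 0.195 − 0.109 = 0.086 | 0.03 to 0.09 SD |
| Equal removal in both arms | difference 0 | 0 |

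A simulation of 4 million draws agreed: 0.032 and 0.107 SD at 5%, 0.058 and 0.194 SD at 10%.

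A simpler calculation gives the same order. If those removed from one arm are δ SD worse than its completers, the completer mean is too favourable by f × δ. With f from 5% to 20% and δ from 0.5 to 1, that is 0.05 × 0.5 = 0.025 to 0.20 × 1 = 0.20 SD.

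**6. Precision.** This is the smaller issue. If rule-driven withdrawals came on top of 10% other loss and only in the MMT arm, power for a 0.42 SD difference against one control would fall from 80% to 78.9% with 5% withdrawn (84.15 versus 89.1 participants) and to 77.6% with 10% withdrawn (79.2 versus 89.1).

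**The case against.** The strongest reply is that this is a journal article, and handling of data after withdrawal is commonly left to the full protocol. The article does not say that withdrawn participants are excluded from analysis or that data already collected are discarded. Being lost to later visits does not in itself breach intention-to-treat. This narrows the point to informative missing data, but it does not remove it: the withdrawal rule is stated explicitly, and a fuller document would have to contradict it.

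Second, the rule can be read as tied to the session, since it concerns adverse events of the intervention. In the other-care rule, withdrawal could mean withdrawal from treatment. Both readings are reasonable. The first softens the absence of a time limit but leaves the consequence unchanged. The second is why the other-care rule is an ambiguity here, not a demonstrated fault.

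Third, the illustration is a stress case. A transient reaction will not correlate perfectly with monthly headache days, so the upper ends are bounds. All arms do the same exercise, so some events will occur in every arm. People with a history of dizziness are excluded. The Discussion states that previous MMT studies "have not reported adverse events associated with its application". All of this stands: the rate may be low and the net bias small.

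Fourth, the 10% drop-out allowance may already include these withdrawals. The article does not say. If it does not include them and the allowance is used up, further withdrawals would take loss past 29.7 of 297, above which the Methods no longer commit to intention-to-treat. If it does include them, that argument and the power figures fall away. The main point does not depend on either.

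**Conclusion.** The concern holds. As written, the adverse-event rule removes randomised participants from the study for events related to the headache outcomes, and the article makes no provision to keep following them. This is at odds with the unconditional intention-to-treat statement in the abstract. The conditional statement in Statistical methods gives weaker protection and does not restore follow-up.

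The size cannot be fixed from the documents. Under the assumptions above, unequal removal of 10% against 5% shifts the contrast by 0.03 to 0.09 SD, and removal of 10% from one arm alone by up to 0.20 SD as an upper bound. Equal removal of similar people gives none. If those removed have worse outcomes, the arm that loses more looks better than it should; which arm that would be is unknown. The wording should be fixed because the correction is simple and avoids the problem whatever the event rate. Confidence is medium, because the event rate is unknown and the wording may be looser than intended.

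**What to change.** In the Interventions section, replace withdrawal from the study with stopping the allocated treatment, with medical referral for adverse events. Apply the same wording to the other-care rule. Then add one statement covering everyone who stops treatment, has an adverse event or uses other therapy:

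- they continue the headache diary and are assessed at 4 weeks, 3 months and 6 months unless they withdraw consent for follow-up;
- they are analysed in the arm to which they were randomised;
- the reason and date of stopping, or of other therapy, are recorded.

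The clinical threshold for stopping treatment stays with the investigators, so participant safety is unaffected.

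The cost is a protocol amendment. The Procedures section already provides the route: "Any change in the protocol will be communicated with the ethics committee", followed by a registry update once approved. Two committees approved the trial. The diary and the visits already exist, so no new data collection is needed.

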This paper aims to report the study protocol which will be used to investigate the short and mid-term effectiveness of MMT and exercise on headache frequency, intensity, disability, and duration as well as medication intake, upper cervical rotation range of motion, PPT and patient satisfaction compared with placebo and exercise and exercise alone in the management of migraine, TTH, and CGH. The objective is to investigate whether MMT with exercise is more effective than placebo MMT with exercise or exercise alone. Our primary hypothesis is that there will be a 50% reduction in headache frequency in the experimental group (MMT with exercise) and recovery is greater than that seen in the 2 control groups (placebo MMT with exercise and exercise alone).

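### Participants with a symptom flare or dizziness are withdrawn from the study, not just from treatment, so outcome data are lost for reasons close to the primary outcome

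*Protocol article*

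**What the plan says.** The rule closes the Technique 5 part of the Interventions section. The trigger is broad and is classed as an adverse event: "Any increase in headache intensity or neck pain for more than 1 h or dizziness during or after the intervention will be documented". The consequence is that "participants will be referred to a medical practitioner of the hospital and withdrawn from the study". No judgement on cause is asked for.

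The opening part of Interventions deals with a similar event differently. There, treatment stops if the participant "has an increase in pain or discomfort due to the treatment". A separate sentence covers outside care: "Additionally subjects will be withdrawn if they receive any other physiotherapy program". The protocol therefore has one phrase for ending treatment and another for withdrawal, and the adverse-event rule uses the second.

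On timing, Interventions states: "Each subject will receive 6 treatment sessions spread over 4 consecutive weeks". Outcomes places the assessments at baseline "as well as at 4 weeks, 3 months and 6 months following treatment commencement". The Abstract states: "The intention-to-treat principle will be followed for statistical analysis". Nowhere does the article provide for assessing a participant who has been withdrawn.

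**The concern.** The trigger occurs after randomisation and is itself a worsening of headache or neck pain, or dizziness. The primary outcome is headache days per month, and headache intensity is a secondary outcome. Taking these participants out of follow-up would tend to leave a better-responding group behind, and the hypothesised 50% reduction under MMT would be judged on those who tolerated the treatment.

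The rate may also differ between arms. Manual force is applied only under MMT; the placebo copies the position without force, and the remaining arm receives exercise alone. A difference in withdrawal between arms would bias the randomised comparison. It also works against the Abstract's commitment to intention-to-treat, since no follow-up value would exist for these participants.

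**Working it through.** **1. The two rules side by side**

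| | Opening of Interventions | Adverse-event rule (end of Technique 5) |
|---|---|---|
| Trigger | Increase in pain or discomfort attributed to treatment | Increase in headache or neck pain beyond 1 h, or dizziness; no attribution asked |
| Consequence | Treatment stops | Referral and withdrawal from the study |

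They can be read as tiers of severity. They diverge for a flare not due to treatment: the first rule leaves treatment running, while the second removes the participant from the study.

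**2. Timing.** The trigger is read here as an event during or after a supervised session. The six sessions lie within weeks 0 to 4, and the first post-baseline assessment is at 4 weeks. Withdrawal for a session reaction therefore normally costs all 3 follow-up assessments.

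**3. The plan's own figures.** Equal allocation (Procedures) gives 297 / 3 = 99 per arm. The 10% drop-out step (Statistical methods) fits 267 / 0.90 = 296.7, rounded up to 297, or 267 / 3 = 89 evaluable per arm. The 267 itself cannot be reproduced, because no SD or control-arm change is given.

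**4. Effect within the MMT arm.** The withdrawn share *w* is an assumption: 2%, 5% and 10% of 99 are about 2, 5 and 10 participants. Suppose those who stay show exactly 50%, and baseline frequency is the same in both subsets. Then

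reduction over all randomised = (1 − *w*) × 50% + *w* × *R*,

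where *R* is the reduction the withdrawn would have shown.

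| *R* (assumed) | *w* = 2% | *w* = 5% | *w* = 10% |
|---|---|---|---|
| 25% improvement | 49.5% | 48.75% | 47.5% |
| No change | 49.0% | 47.5% | 45.0% |
| 20% worsening | 48.6% | 46.5% | 43.0% |

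**5. Effect on the between-arm contrast.** Let the withdrawn be *d* SD worse than those who stay, with *d* equal in both arms. Then shift = (*w*₁ − *w*₀) × *d*, where 1 is MMT and 0 a control arm. The standard error with 89 per arm is √(2/89) = 0.150 SD.

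| Withdrawn, MMT vs control (assumed) | *d* = 0.5 | *d* = 1.0 |
|---|---|---|
| 5% vs 1% | 0.02 SD (0.13 SE) | 0.04 SD (0.27 SE) |
| 10% vs 2% | 0.04 SD (0.27 SE) | 0.08 SD (0.53 SE) |
| Equal rates | 0 | 0 |

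For 10% against 2%, a completers-only pairwise test starting from 99 per arm would have a two-sided type I error of about 5.9% (*d* = 0.5) to 8.5% (*d* = 1.0) instead of 5%. If the control arm loses more, the sign reverses.

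**6. How small a session risk produces these rates.** Assuming independent sessions, a 1% chance per session gives 1 − 0.99⁶ = 5.9% over six, and 2% gives 1 − 0.98⁶ = 11.4%.

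**7. Use of the drop-out allowance.** The allowance is 10% of 297 = 29.7. A 5% rate in all arms takes 14.85, half of it.

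**The case against.** The article may simply be using loose wording. The sentence on outside physiotherapy begins as a continuation of the treatment-stopping list, the text never says outright that assessments end, and a condensed article may leave procedures after discontinuation to the full protocol. The Discussion says earlier studies of MMT at the upper cervical spine reported no adverse events, the technique is meant to be pain-free, and Techniques 1 to 3 are repeated only if headache falls at the first application. If no attribution is needed, ordinary headache fluctuation would trigger the rule in every arm, and with equal rates and severity the contrast does not move. A brief session reaction, or dizziness, need not predict more headache days.

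Much of this stands as a limit on size. It makes 10% against 2% less likely, and the direction of bias is an assumption. It does not remove the problem. The wording is a stated rule, not an omission, and its plain meaning is that participation ends. A record of no reported events does not settle the rate under so broad a definition, in people who have headache at least weekly and whose headache is reproduced by palpating the upper neck (Eligibility criteria). How missing values are handled can be left to an analysis plan; whether they are collected cannot. Statistical methods makes intention-to-treat conditional on the amount of loss. That is a separate matter, and this point holds under either statement.

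**Conclusion.** The concern holds. Followed as written, the adverse-event rule removes all post-baseline data for participants selected after randomisation by a symptom close to the primary outcome. The likely effect is small at low event rates and moderate at most: 0.02 to 0.08 SD on the contrast in the scenarios shown, and a fall from 50% to between 43.0% and 49.5% in the MMT arm's reduction. Event rates, the gap between withdrawn and retained participants, and the direction are all assumptions, since the documents give none of them. With equal rates and severity, only power is lost. The rule should be changed because the loss is avoidable at little cost, not because a large bias has been shown.

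**What to change.** In the adverse-event rule, replace withdrawal from the study with wording such as: *treatment is stopped and the participant, unless consent is withdrawn, continues with the 4-week, 3-month and 6-month assessments and is included in the intention-to-treat analysis.* Keep the adverse-event record, the medical referral, and the existing stops for withdrawn consent and contra-indications.

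The cost is one sentence and up to 3 assessments per affected participant. The sample size stays at 297. Safety is not weakened: the treatment stop is no narrower, and the unblinded therapist need not judge cause. The headache diary and questionnaires involve no physical contact, and pressure pain threshold and the flexion-rotation test can be skipped if the medical practitioner advises it. If the sponsor meant withdrawal from treatment only, the same sentence says so.
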